### Outcome measures and endpoints

#### Demographic variables

Descriptive data will be reported before treatment (baseline) of all participants regarding age, sex, body mass index, dominant arm, job and whether they smoke or not (by the question; do you smoke?). The jobs of the subjects will be classified according to the International Standard Classification of Occupations (ISCO-08).

#### Primary outcome

The main outcome measures are the changes in pain using a Visual Analog Scale (VAS, 0–100) [9]. The VAS consists of a 100-mm horizontal numbered line anchored at one end (0) with the words “no pain” and at the other end (100) with the words “worst pain imaginable.” Patients are asked to score their pain on this line during rest (at time of measure), provocation and maximum grip strength. The provocation test is conducted on the outpatient clinic by resisted dorsiflexion of the wrist during full elbow extension. The VAS pain scores will be measured at baseline and 8 weeks, 5 months and 1 year after treatment.

The main outcome measure is the change in VAS when performing the provocation test 5 months after treatment.

#### Secondary outcomes

Secondary outcome measures are quality of life and functional recovery. Assessments will be made at baseline and 8 weeks, 5 months and 1 year after treatment. For the functional recovery a physical examination is conducted of the affected arm compared to the healthy arm by an orthopaedic surgeon or trained resident. Table 2 shows the items scored at baseline with physical examination. At the 8 weeks and 5 months follow-up visits, a specialized nurse, physiotherapist, trained resident or orthopaedic surgeon (depending on the hospital the patient is treated) will perform a physical examination of both elbows (Table 1). To assess the functional recovery, work ability and patients’ subjective experience on function pain and quality of life the patients are asked to complete a number of questionnaires (Table 2).

**Table 1 Tab1:** Physical examination

Test	Gradation
At baseline	
Valgus stability	Grade 1/2/3
Pivot shift	Positive/negative
Position of the axis	Normal/valgus/varus
Motor function and sensibility of the ulnar nerve	Intact/disturbed
At baseline, 8 weeks and 5 months	
ROM; Flexion/extension, pronation/supination. Measured by classic goniometry	In degrees
Hydrops	Yes/no
Pain on palpation epicondyle and ECRB;	Yes/no
Pain during dorsiflexion of the wrist (from a neutral position and elbow straight) against resistance	Yes/no
Strength; maximum voluntary hand force measured with a Jamar manual force meter [20]	In Kilogram
Strength; ratio between the affected and healthy arm is calculated. Three consecutive measurements will be performed with one minute intervals between contractions.	In Kilogram The average force of three repetitions will be calculated

**Table 2 Tab2:** Overview of questionnaire used to assess the functional recovery, work ability and patients subjective experience on function pain and quality of life. The questionnaires will be completed at baseline, 8 weeks, 5 months and 1 year after treatment

Measures	Questionnaires	Scores	Reliability and validity	Population
Physical function and symptoms	Quick-DASH [10–12]	0 (no disability) to 100 (most severe disability)	Cronbach α > or = 0.92 and an ICC^a^ > or = 0.94. validity was established (r > or = 0.64	Patients with various upper-limb conditions
Patients’ subjective experience of elbow surgery on elbow function, pain, and Quality of life	Oxford Elbow score [13]	0 (unsatisfactory joint function)to 48 (satisfactory joint function)	Cronbach’s α coefficients for the function, pain and social-psychological domains respectively 0.90, 0.87 and 0.90,. ICC 0.87 for function, 0.89 for pain and 0.87 for social-psychological.	Patients after elbow trauma and surgery
Functional recovery	The WORQ-UP questionnaire for the upper limb [14]	0 (no disability) to 102 (most severe disability)	-	Patients with elbow complaints
Pain and functional ability	The Dutch Patient-Rated Tennis Elbow Evaluation PRTEE-D [15]	Pain subscale (0 = no pain, 10 = worst imaginable). function subscale (0 = no difficulty, 10 = unable to do)	Crohnbach’s α 0.98 and 0.93 for the pain subscale and 0.97 for the function subscale. ICC 0.98 and 0.97 for pain and function scale	Patients with LE
Work ability	The first question on work ability of the Work Ability Index amended for elbow pain “current work ability compared with the lifetime best regarding your elbow complaints”, [16–18]	0 (completely unable to work) to 10 (work ability at its lifetime best)	Acceptable test-retest reliability and predictive validity for return to work	Construction workers with and without musculoskeletal complaints of the upper extremity, lower back, and lower extremity
Generic measure of health gain, as a derivative of quality of life	Quality adjusted life years (EQ-5D/QALYs) [19]	a year of life lived in perfect health is worth 1 QALY and a year of life lived in a state of less than this perfect health is worth less than 1.	validated, no studies on reliability	General population sample

^a^*ICC* The intra-class correlation coefficient

The 1-year follow-up moment will be conducted by email or, if necessary, by telephone by a trained investigator. The patient will be asked to complete the questionnaires mentioned above. All complications and/or co-interventions will be registered.

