To get a better understanding, a linear mixed model analysis will be performed with the three repeated measurements of pain VAS as dependent variables. Along with treatment (a three-level nominal variable) the following covariables will be included in the model as independent variables: baseline pain VAS, the binary variable perceived aggravation of pain due to work ((totally) agree vs otherwise) and a three-level nominal variable time (visit number). Moreover, the interaction between treatment and time will be tested. If this interaction is not significant at the 0.01 level, then one overall treatment effect will be estimated assuming parallelism of the treatment effect. If this interaction turned out to be significant at the 0.01 level, then the effect of the 5 months’ visit will be considered the main effect of interest. Effects will be quantified by estimating two-sided 98% confidence intervals of the pair wise mean differences in pain VAS between the three treatment groups. Equivalence between two treatments is accepted if such a confidence interval is totally overlapped by the interval − 10 + 10. A restricted maximum likelihood estimation method will be used to estimate the coefficients so that missing values are properly imputed in order to meet the itt-condition. Under the pp-condition only patients with non-missing observations will enter the linear mixed model.

Similar analysis will be performed for functional recovery and quality of life. Otherwise the descriptives of the secondary outcome measures will be reported for the three groups.

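### The plan uses a 1-year pain VAS in the mixed model and per-protocol set without naming the VAS condition, and the primary provocation VAS cannot be obtained at the remote 1-year contact as described

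*Protocol article*

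**What the plan says.** All references are to the protocol article.

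- *Primary outcome* fixes the endpoint: "The main outcome measure is the change in VAS when performing the provocation test 5 months after treatment". Three VAS conditions are collected: "Patients are asked to score their pain on this line during rest (at time of measure), provocation and maximum grip strength". The setting of the test is explicit: "The provocation test is conducted on the outpatient clinic by resisted dorsiflexion of the wrist during full elbow extension". The schedule is "The VAS pain scores will be measured at baseline and 8 weeks, 5 months and 1 year after treatment".
- *Secondary outcomes*, Table 1, lists pain on resisted dorsiflexion and Jamar grip strength under the line "At baseline, 8 weeks and 5 months". No examination is listed for 1 year.
- *Secondary outcomes*, below Table 2, describes the last contact: "The 1-year follow-up moment will be conducted by email or, if necessary, by telephone by a trained investigator". Its content is given as "The patient will be asked to complete the questionnaires mentioned above", plus registration of complications and co-interventions. Table 2 does not list the pain VAS.
- *Statistical analysis* limits the per-protocol set to patients with a pain VAS at 8 weeks, 5 months and 1 year. It specifies a linear mixed model "with the three repeated measurements of pain VAS as dependent variables". If treatment-by-time is not significant at 0.01, one treatment effect over all visits is estimated; if it is significant, the 5-month effect becomes the main one. Neither rule names the VAS condition.

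**The concern.** The endpoint is defined by a test done in the clinic, the last follow-up is remote, and two analysis rules depend on a pain VAS from that follow-up. These statements cannot all hold for the provocation VAS.

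Two things are at stake. The first is whether the per-protocol set can be formed as written. The second is what the default treatment effect estimates. The endpoint is a 5-month contrast, but the mixed model reports that contrast as the main effect only after a significant interaction. Otherwise the reported effect averages over a visit at which the primary variable is not described as obtainable. The ±10 mm equivalence rule is applied to the intervals from this model, so the choice reaches the trial's conclusion.

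**Working it through.** The plan states no figure to reproduce on this point. The check compares the schedule with the analysis, then sizes the 1-year value's share of the pooled effect.

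**Step 1. What can exist at each time, as described**

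| Time | Contact | Rest VAS | Provocation VAS | Grip VAS |
|---|---|---|---|---|
| Baseline | clinic | yes | yes | yes |
| 8 weeks | clinic | yes | yes | yes |
| 5 months | clinic | yes | yes | yes |
| 1 year | email or telephone | possible | no test described | no test described |

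No self-administered provocation test at home is described.

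**Step 2. Consequence under each reading of pain VAS**

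- Provocation: the model has two follow-up visits, and 0 of 165 patients can meet the three-visit per-protocol rule.
- Rest throughout: all three values can exist, but the model does not analyse the primary outcome.
- Provocation in clinic and another score at 1 year: three values exist, but they are not the same variable.

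**Step 3. Weight of the 1-year value in the pooled effect**

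With complete data, equal variances and residual correlation matrix R, the weights are R⁻¹1 / (1ᵀR⁻¹1).

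- Compound symmetry: 1/3 for each visit, whatever the correlation.
- AR(1) with visits treated as equally spaced: 1/(3 − ρ) for the first and last visits and (1 − ρ)/(3 − ρ) for the middle one. For assumed ρ = 0.3, 0.5 and 0.7, the 1-year weight is 0.37, 0.40 and 0.43, and the 5-month weight is 0.26, 0.20 and 0.13.

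**Step 4. Shift if the substitute separates the arms less**

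Assume, for illustration only, a provocation difference of 10 mm at 8 weeks and 5 months, and a difference of 10f at 1 year. With equal weights the pooled effect is 10(2 + f)/3:

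- f = 1: 10.0 mm
- f = 0.5: 8.3 mm
- f = 0: 6.7 mm

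With a 1-year weight of 0.43, 10[1 − 0.43(1 − f)] gives about 7.8 mm (f = 0.5) and 5.7 mm (f = 0).

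**Step 5. How far the interaction test protects**

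The SD is not stated. *Sample size and power calculation* gives 47 per arm, a 10 mm difference and two-sided alpha of 2%. Under an assumed 80% power, a superiority calculation implies SD = 10√(47/2)/(2.326 + 0.842) = 15.3 mm. I use this as the residual SD, with compound symmetry. If one arm differs from the other two and its contrast falls by L mm at 1 year, the 4-df interaction test has non-centrality n(4/9)L²/[SD²(1 − ρ)] and critical value 13.28.

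- L = 5 (f = 0.5), ρ = 0.5: 47 × (4/9) × 25 / (234.1 × 0.5) = 4.46, power about 16%. For ρ = 0.3 and 0.7: about 10% and 33%.
- L = 10 (f = 0), ρ = 0.5: non-centrality 17.85, power about 83%. For ρ = 0.3 and 0.7: about 64% and 98%.

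On these assumptions the test usually catches a complete loss of contrast and usually misses a halving.

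**The case against.** **The primary endpoint is unaffected.** It is set at 5 months, when patients are examined in clinic. This stands: a reader might infer that the primary outcome cannot be measured, and the text does not support that.

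**The per-protocol set need not be empty.** Rest pain could be requested remotely, and the analysis rules say only pain VAS. Separate models per condition are also possible. This stands as a limit: the set is empty only if the provocation VAS is meant. It does not remove the conflict, because the unnamed condition is what leaves every reading open. The main analysis is by intention to treat and does not depend on that set.

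**A lower 1-year pain level does no harm in itself.** Time enters the model as a three-level factor and absorbs a uniform shift. This stands. Only a different between-arm contrast matters, and the documents do not show that rest pain has a smaller one.

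**A false finding of equivalence is not shown.** A reader might infer one from a pooled value inside ±10. The plan requires the whole 98% interval to lie inside. With SD 15.3 and 47 per arm, the single-visit half-width is 2.326 × 15.3 × √(2/47) = 7.3 mm. Averaging three visits at ρ = 0.5 multiplies it by √(2/3), giving about 6.0 mm. A pooled 8.3 or 6.7 mm would not meet the rule. Step 4 shows direction only.

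**The model's standing is debatable.** It is introduced as giving better understanding, after t-tests and a 98% interval. But the pooling and equivalence rules are attached to it, so its outcome still has to be defined.

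**A condensed article may leave detail to the full protocol.** That would excuse silence. Here the article makes statements that do not fit together.

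**Conclusion.** The point holds as a conflict between the measurement schedule and two analysis rules. As described, a provocation VAS cannot be obtained at 1 year. Either the three-visit per-protocol rule cannot be met and the model has two follow-up visits, or another pain score enters.

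In the second case that score carries one third of the default pooled effect under compound symmetry, or 0.37 to 0.43 under AR(1) with assumed correlation 0.3 to 0.7. The estimate moves toward zero only if the substitute's contrast is smaller, which is an assumption. The 0.01 interaction test is then a partial safeguard: about 10% to 33% power against a halved contrast and 64% to 98% against a lost one, given an assumed SD of 15.3 mm and compound symmetry.

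The 5-month endpoint is sound as a measurement. The damage is confined to the pooled effect, the interaction test and the per-protocol set.

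**What to change.** Reconcile *Primary outcome*, *Secondary outcomes* (Table 1 and the description of the 1-year contact) and *Statistical analysis*:

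1. Name the VAS condition wherever the analysis refers to pain VAS.
2. Fit the provocation-VAS model to 8 weeks and 5 months, with the 5-month contrast as the main effect whatever the interaction test shows. This matches the endpoint already declared.
3. Define the per-protocol set on the 5-month provocation VAS.
4. Analyse any remotely collected 1-year pain score separately as a secondary outcome.
5. Correct the VAS schedule to state which conditions are collected at 1 year. The documents do not settle this, so the sponsor must. If a 1-year clinic test is in fact done, the description of that contact and Table 1 should say so.

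Items 1 to 4 cost wording only and need no extra visit. The small downside is that the 1-year value no longer contributes to the main model.

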#### Crossover

Patients treated with perforation without infiltration which could not be classified as “success” should also be treated with infiltration with autologous blood, a so called one arm crossover. This is currently the most common treatment of LE in OLVG and Amphia hospital. A treatment is classified as a success when there is a reduction of pain of 10 points (0-100 mm VAS score) 5 months after the treatment compared with baseline. If the treatment wasn’t successful after 5 months the given treatment can be looked up in an encrypted list; this list only shows if the patient has had an infiltration or perforation, without the specification of the injectable. After the crossover moment, patient data will be collected as described above.

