#### Blinding

The treatment will be blinded for both the patient and outcome assessor (the specialized nurse, physiotherapist or trained resident). During the injection the patient will be blinded. Injectables will be blinded by a supporting nurse through the use of an opaque tape. The outcome assessors are different for each participating center. However, the outcome assessors are always blinded during all the follow up visits. The physician who performs the perforation does not have to be blinded, as long as he or she does not perform the follow-up visits.

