### Statistical analysis

To compare groups the three groups (A – B, A – C and B - C) Chi-square tests will be used for categorical variables, and independent t-tests for continuous variables. The primary aim is to assess whether the reduction in pain for perforation with application of autologous blood or dextrose is more than 10 points compared to perforation only.

If so, a comparison will be made between the reduction in pain for perforation with application of autologous blood versus dextrose. A mean and a two-sided 98% confidence interval will be calculated. A mixed model will be used taking into account effects of time and treatment. The analyses are primarily performed according to the intention-to-treat principle.

In detail, data will be analyzed in the per protocol (pp) set as well as in the intention-to-treat (itt) set of patients. The pp-set consists of all patients, categorized according to the treatment eventually received, with non-missing observations on the pain VAS at all three visits during follow-up (8 weeks, 5 months and 1 year). The itt-set consists of all randomized patients.

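### One-way crossover to blood after 5 months is pooled into the intention-to-treat effect, so the 1-year contrast, and to a lesser degree the overall effect, no longer estimates perforation only versus blood

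*Protocol article*

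**What the plan says.** **Crossover section.** Perforation-only patients not classed as a success "should also be treated with infiltration with autologous blood, a so called one arm crossover". The trigger is the 5-month result: "A treatment is classified as a success when there is a reduction of pain of 10 points" compared with baseline. No corresponding step is described for unsuccessful patients in the blood or dextrose arms. For unsuccessful patients a list may be consulted, and "this list only shows if the patient has had an infiltration or perforation, without the specification of the injectable". Follow-up then continues: "After the crossover moment, patient data will be collected as described above".

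**Primary outcome section.** "The main outcome measure is the change in VAS when performing the provocation test 5 months after treatment". This precedes the crossover.

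**Statistical analysis section.** "The analyses are primarily performed according to the intention-to-treat principle", and "The itt-set consists of all randomized patients". The linear mixed model takes the VAS at 8 weeks, 5 months and 1 year. If the treatment-by-time interaction is not significant at 0.01, one overall treatment effect is estimated; otherwise the 5-month effect is the one of interest. Equivalence is accepted when the 98% confidence interval lies wholly within −10 to +10. Similar analyses are planned for function and quality of life. The per-protocol set groups patients by the treatment they eventually received. No term, censoring rule or separate estimand covers the crossover.

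**Blinding section.** "the outcome assessors are always blinded during all the follow up visits", with no exception after the look-up.

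**The concern.** At 1 year the perforation-only arm has become perforation, followed by blood if it failed. The blood arm has no such second step. An intention-to-treat contrast at that visit is a legitimate comparison of two strategies, but it does not answer the primary objective, which is perforation only against perforation with a fluid. The plan nevertheless feeds that visit into the effect on which the equivalence rule is applied, and the Background states a hypothesis of no difference. If crossed-over patients gain what blood adds, the contrast shrinks towards that hypothesis.

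The per-protocol set does not offer a clean alternative. Read literally, grouping by treatment eventually received moves perforation-only patients selected for poor response into the blood group.

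There is also a masking problem. VAS and questionnaires are patient-reported, and the 1-year follow-up is done by email or telephone. A patient who failed and was then offered blood, or was not offered it, can infer whether the first procedure included an infiltration.

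**Working it through.** **Inputs from the protocol.** Crossover in one arm only, triggered by a reduction of less than 10 points at 5 months; three visits in the model; interaction tested at 0.01; margin ±10; 98% interval; 47 evaluable patients per arm (55 randomised).

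**Inputs not given.** SD, correlation between visits, true effect, expected share crossing over and gain after crossover. The values below are assumptions. The planned 47 per arm cannot be reproduced, because neither SD nor power is stated. With a 10 mm difference and two-sided 2% alpha it implies SD = 10 × √(47/2) / (2.326 + 0.842) = 15.3 at 80% power, or 13.4 at 90%.

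**Formulas.** Let d be the true VAS difference (perforation only minus blood), f the share of the perforation-only arm that crosses over, and g their mean gain from it.

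- 5-month contrast: d
- 1-year contrast: d − f·g
- Equal-weight average over three visits: d − f·g/3

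**Main illustration.** d = g = 12, mean change with blood −25 or −35 (so −13 or −23 with perforation only), SD of change 20 or 25, normal distribution. Then f = P(change > −10).

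| Mean change, blood | SD | f | 1 year: 12(1 − f) | Average: 12 − 4f |
|---|---|---|---|---|
| −25 | 20 | P(Z > 0.15) = 0.44 | 6.7 | 10.2 |
| −25 | 25 | P(Z > 0.12) = 0.45 | 6.6 | 10.2 |
| −35 | 20 | P(Z > 0.65) = 0.26 | 8.9 | 11.0 |
| −35 | 25 | P(Z > 0.52) = 0.30 | 8.4 | 10.8 |

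Simulation with correlation 0.5 agrees: about 6.5 to 9 mm at 1 year and 10.2 to 11 mm for the average.

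**Does this trigger the equivalence rule?** The rule needs the whole interval inside ±10. With 47 per arm the unadjusted 98% half-width at 1 year is 2.326 × SD × √(2/47), which is 9.6 mm for SD 20 and 12.0 mm for SD 25. In simulation, equivalence is declared at 1 year in at most about 4% of trials with 47 per arm (up to about 7% with 55), and on the three-visit average in fewer than 1%.

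**A setting closer to the margin.** d = 10, SD 15.3, g = 10, 47 per arm, baseline-adjusted. Without crossover, equivalence is declared in about 1% of trials.

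| f | 1-year contrast | Equivalence at 1 year | Equivalence under the plan's pooling rule | Interaction significant |
|---|---|---|---|---|
| 0.26 | 7.5 | 0.08 | 0.024 | 3% |
| 0.50 | 5.1 | 0.29 | 0.052 | 15% |

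In these settings the interaction test seldom keeps the post-crossover visit out of the overall effect. The 5-month contrast stays at 10 in each case.

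**The opposite direction.** d = 0, g = 20 (a second procedure helps in itself), f = 0.26, SD 15.3: the 1-year contrast is 0 − 0.26 × 20 ≈ −5 in favour of perforation only. The chance of declaring equivalence at 1 year drops from about 0.82 to 0.27.

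**Per-protocol, read literally.** Moving crossed-over patients into the blood group in the main illustration gives a 1-year contrast of about −0.4 to 5 mm where the truth is 12.

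**Setting post-crossover values to missing.** Conditioning on the 8-week and 5-month VAS recovers 11.9 to 12.2 mm in the main illustration. The data were generated from a linear normal model in which the observed 5-month VAS alone drives crossover, so this shows that the method works under its assumption, not that the assumption holds.

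**The case against.** The strongest reply is that the primary endpoint is at 5 months, before anyone crosses over, and that the plan announces no 1-year equivalence claim. That stands for the 5-month contrast. It does not cover the pooled effect, which is the default result of the mixed model and includes the 1-year visit.

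A second reply is that a 1-year point estimate inside ±10 is not a declaration of equivalence, because the whole interval must fall inside. That is correct. A reader might infer that the plan will produce a false equivalence conclusion; the calculations do not support this for the pooled effect. A reader might also infer that the crossover always pulls towards equivalence. It does so only if crossed-over patients gain about what blood adds.

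Third, a per-protocol analysis is planned, so crossover is not wholly ignored. True, but its grouping adds a selection bias of its own.

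Fourth, on blinding, the Crossover section says the list can be looked up, not that patients are told the entry, and the sentence in the Blinding section concerns assessors. A reader might infer that patients are unblinded by the protocol itself; the text supports only that they can work it out from what they are offered.

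Fifth, the sentence on data collection after crossover might be read as restarting the visit clock, which would put a crossed-over patient's 1-year visit at about 17 months. The Study design section fixes a 12-month follow-up, so this is an ambiguity to settle, not an established fault.

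Finally, sensitivity analyses are often left to an analysis plan that is not shown here. That explains silence, but the protocol is not silent: it specifies the visits, covariates, pooling rule and margin, and these put post-crossover values into the treatment contrast.

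**Conclusion.** The point holds as a biased estimate under a stated rule. The direction depends on g: towards no difference when crossed-over patients gain what blood adds, and possibly past zero in favour of perforation only when a second procedure itself helps. For a true 12 mm difference and the assumed inputs, the loss is roughly 3 to 5.5 mm at 1 year and 1 to 2 mm in the three-visit average. The same applies to function and quality-of-life scores analysed in the same way.

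The 5-month result is sound in this respect, and no false conclusion has been shown. In the setting nearest the margin, the chance of wrongly declaring equivalence under the pooling rule rises from about 1% to between 2% and 5%. It reaches about 8% only if half the arm crosses over and gains 20 mm. All these sizes rest on an SD, correlation, effect and gain that the protocol does not supply. Blinding of patient-reported outcomes is not assured after 5 months. The change is worth making because it costs little and the Crossover, Blinding and Statistical analysis sections do not fit together as written.

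**What to change.** Leave the crossover itself as it is, and change the analysis and wording:

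1. Base the primary effect and the ±10 rule on the 5-month contrast, from a model of data up to 5 months.
2. Report the 1-year intention-to-treat contrast as a secondary comparison of strategies, with visits timed from first treatment.
3. Add a 1-year sensitivity analysis with post-crossover values set to missing. State its missing-at-random assumption. State also which VAS score (rest, provocation or grip) triggers crossover, since the Crossover section does not say and the assumption depends on it. If nearly all failures cross over, say that the result extrapolates.
4. In the per-protocol set, do not count post-crossover values as blood-arm data.
5. Record each patient's 5-month outcome before that patient's list entry is consulted. Locking all patients' 5-month data first would delay the crossover and is not needed.
6. Limit the blinding claim to the period up to 5 months.

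The cost is revised wording and one additional model. Claims at 1 year become more modest, and 1-year data no longer add precision to the primary effect.
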